### 6.4.2 Immunization and Follow-Up Plan

The Phase Ib clinical trial requires a total of 36 volunteers, including those who have and have not previously received the smallpox vaccine. These volunteers will be divided into three groups: a combined immunization group (24 individuals) receiving three doses of the DNA vaccine and one dose of the rTV vaccine, a DNA-only group (6 individuals) receiving three doses of the DNA vaccine alone, and a placebo group (6 individuals) receiving only a placebo. The combined immunization group is further divided into a low-dose and a high-dose subgroup, each consisting of 12 individuals. Recruitment will aim to include an equal number of individuals who have and have not received the smallpox vaccine in each

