### **6.10.2 Sample Size**

In accordance with the clinical trial approval requirements of the China Food and Drug Administration, this Phase Ib study will enroll 36 healthy volunteers to receive the DNA-rTV vaccine.

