### (3) Safety and Tolerability Evaluation:

Descriptive analysis will be used for safety evaluation, including vital signs (blood pressure, pulse, temperature, respiration), physical examinations, complete blood counts, blood biochemistry, and other laboratory tests at each follow-up period. Repeated measures ANOVA will be used for statistical comparison of measurement indicators across different follow-up periods. Electrocardiogram (ECG) results will list the status at each follow-up period and changes before and after the trial, along with a list of subjects with abnormal results.

Descriptive analysis will be performed for adverse events and adverse reactions (definitely related, possibly related, or indeterminable to vaccination) during the trial. For adverse events and reactions with higher incidence rates, the chi-square test will be used for statistical comparison; for those with very low incidence rates, statistical testing based on the Poisson distribution will be conducted.

Subjects included in the safety analysis must meet the following criteria:

- Meet all inclusion and exclusion criteria.
- Receive at least one dose of the vaccine.

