### (4) Immunogenicity Evaluation:

Immunogenicity evaluation will primarily be descriptive, reporting the positive rates of humoral and cellular immune responses.

For the Phase Ib study, differences in immunogenicity among different vaccination doses (combined immunization vs. DNA-alone), smallpox vaccination history, and study groups (vaccine vs. placebo) will be compared using logistic regression. The outcome variable (Y) will be the presence or absence of humoral/cellular immunity, with independent variables including vaccination dose (high vs. low), immunization strategy (combined vs. DNA-alone), smallpox vaccination history (vaccinated vs. unvaccinated), and study group (vaccine vs. placebo). For immune response intensity indicators such as antibody titers and Elispot counts, repeated measures ANOVA will be used. If the data do not meet the conditions for repeated measures ANOVA, appropriate data transformations will be applied.

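### The safety analysis set excludes dosed participants who fail an eligibility criterion, which can lower the reported primary safety rates; its wording also omits placebo recipients, probably by accident

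*Protocol*

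**What the plan says.** Section 6.10.5 (3) of the protocol opens its definition with "Subjects included in the safety analysis must meet the following criteria" and then lists two conditions: "Meet all inclusion and exclusion criteria" and "Receive at least one dose of the vaccine". Both are mandatory, and no other section defines a wider safety set.

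Safety is the primary objective (6.1). The primary safety events are grade 3 or higher local and systemic reactions and vaccine-caused stops to the schedule (6.2.1.1). Table 3 turns these into the proportion of participants with grade 3 or higher adverse events, by group.

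The groups in 6.4.2 are "a combined immunization group (24 individuals) receiving three doses of the DNA vaccine and one dose of the rTV vaccine", split into two dose subgroups of 12; "a DNA-only group (6 individuals) receiving three doses of the DNA vaccine alone"; and "a placebo group (6 individuals) receiving only a placebo".

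The closing paragraph of 6.4.1 gives the purpose of the criteria: they protect participants and the results by keeping out people at greater risk of adverse events and people whose conditions could disturb the outcomes.

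**The concern.** A safety rate should describe everyone exposed. Here a participant can be dosed, have an adverse event, and then leave both numerator and denominator because an eligibility criterion turns out not to have been met. If the criteria do what 6.4.1 says, the people removed tend to be those more likely to have events, so removal lowers the rate.

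Late findings of ineligibility are foreseeable. Monitors are asked during the trial to confirm that enrolled participants are eligible (7.3.3). Several exclusions in 6.4.1 concern close contacts in the month after rTV vaccination, so their status can be settled only after dosing. History-based exclusions such as eczema can be missed at screening.

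The arms have 12 or 6 participants, so a single removal can change a report of one severe reaction into a report of none. Separately, the dose condition mentions vaccine only, which leaves the status of the placebo group to interpretation.

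**Working it through.** **1. The protocol's own figure.** The arms in 6.4.2 sum to 12 + 12 + 6 + 6 = 36, which matches 6.10.2. Section 6.10.3 randomizes 18 participants per phase at 2:1, giving 18 × 2/3 = 12 and 18 × 1/3 = 6 in each phase. This agrees.

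**2. Who is in the safety set as written.**
- Eligibility condition: any dosed participant found ineligible is out. The protocol gives no expected number.
- Dose condition, read literally: the 6 placebo recipients receive no vaccine, so at most 36 − 6 = 30 remain (12/12/6/0).

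**3. Effect of one removal on an observed rate (assumed counts).** The intervals are exact Clopper-Pearson 95% limits for x events in n: the lower limit is the 0.025 quantile of Beta(x, n − x + 1), or 0 when x = 0; the upper limit is the 0.975 quantile of Beta(x + 1, n − x).

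| Situation | All dosed | Ineligible participant removed |
|---|---|---|
| Arm of 12, one event, in the ineligible participant | 1/12 = 8.3% (0.2% to 38.5%) | 0/11 = 0% (0% to 28.5%) |
| Arm of 12, two events, one in the ineligible participant | 2/12 = 16.7% (2.1% to 48.4%) | 1/11 = 9.1% (0.2% to 41.3%) |
| Arm of 6, one event, in the ineligible participant | 1/6 = 16.7% (0.4% to 64.1%) | 0/5 = 0% (0% to 52.2%) |

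**4. Expected bias (assumed risks).** With k ineligible participants at risk q and the other 12 − k at risk p, the true arm rate is [(12 − k)p + kq]/12, while the restricted set estimates p. Take p = 5%:
- k = 1, q = 20%: (11 × 5% + 20%)/12 = 6.25%, against 5% estimated.
- k = 1, q = 50%: (11 × 5% + 50%)/12 = 8.75%, against 5%.
- k = 2, q = 20%: (10 × 5% + 2 × 20%)/12 = 7.5%, against 5%.
- k = 2, q = 50%: (10 × 5% + 2 × 50%)/12 = 12.5%, against 5%.
- q = 5%: the true rate is 5%, so there is no expected bias.

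The direction thus depends on q exceeding p, which is what 6.4.1 implies for the criteria as a whole.

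**5. Is the placebo omission intended?** Four places point the other way. Table 3 calls for the proportions in every group. Section 6.10.2 says "this Phase Ib study will enroll 36 healthy volunteers to receive the DNA-rTV vaccine", which counts the placebo arm among vaccine recipients. Section 6.10.4 describes participants as being vaccinated with either product. Section 6.10.5 (2) includes the placebo group in the baseline comparison. Together they suggest that dose of vaccine was used loosely for any study injection.

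**The case against.** The strongest reply is that the rule affects reporting, not protection. All adverse events go into the case report forms and database, serious events are reported within 24 hours and grade 3 events within 2 working days (6.5.7). The halting rules count vaccine-related events of grade 3 or higher without reference to this set (6.4.2, 6.7.2), and an independent board meets every two months (7.3.1). This stands: a reader might infer that the trial would fail to detect such events, but the documents do not support that.

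A reader might also infer that the plan discards its control arm. Step 5 of the working argues against this. Even on the literal wording, the DNA-only group receives rTV placebo and remains the randomized comparator for the high-dose group; what would be missing is the comparator for DNA itself and for the low-dose group.

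A third inference is that ineligibility would mostly come to light while a severe event is being investigated, making removal depend on outcome. That is possible, but nothing in the protocol establishes it. The laboratory criteria are tested at screening, and eligibility is confirmed before enrolment (6.3, Table 6). Some criteria, such as recent participation in another trial, have no evident link to vaccine risk.

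Finally, the intervals in step 3 overlap heavily, the safety analysis is mainly descriptive, and no power calculation uses this set. All true, but none of it gives a reason to leave exposed participants out of a safety rate.

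**Conclusion.** The eligibility condition is wrong as written for a safety analysis. It can remove dosed participants and their events from the primary safety rates, with a downward direction that follows from the stated purpose of the criteria. In the illustration, one affected participant takes a 12-person arm from 8.3% to 0%. The size rests on assumed counts and risks: the number of dosed but ineligible participants is unknown, may be zero, and if their risk equals that of the others there is no expected bias. The harm is limited to the final summary rates and group comparisons.

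The omission of placebo from the dose condition is a wording fault to correct in the same edit, not evidence of a planned loss of the control arm. A statistical analysis plan, not available here, might define a wider set, but it would then conflict with a rule that the protocol has already fixed.

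**What to change.** Replace the two conditions in 6.10.5 (3) with one: the safety set is all participants who received at least one dose of study vaccine or placebo, analysed by the product actually received and regardless of eligibility. List dosed participants with eligibility deviations separately, with their adverse events. If an eligibility-restricted set is wanted, use it only as a per-protocol set for immunogenicity. Carry the same definition into the statistical analysis plan. The cost is about two lines of text; no extra data, visits or participants are needed.

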### (4) Immunogenicity Evaluation:

Immunogenicity evaluation will primarily be descriptive, reporting the positive rates of humoral and cellular immune responses.

For the Phase Ib study, differences in immunogenicity among different vaccination doses (combined immunization vs. DNA-alone), smallpox vaccination history, and study groups (vaccine vs. placebo) will be compared using logistic regression. The outcome variable (Y) will be the presence or absence of humoral/cellular immunity, with independent variables including vaccination dose (high vs. low), immunization strategy (combined vs. DNA-alone), smallpox vaccination history (vaccinated vs. unvaccinated), and study group (vaccine vs. placebo). For immune response intensity indicators such as antibody titers and Elispot counts, repeated measures ANOVA will be used. If the data do not meet the conditions for repeated measures ANOVA, appropriate data transformations will be applied.

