#### **6.10.7 Treatment of Missing Values**

In statistical analysis, missing values will not be imputed. Unless otherwise specified, all results are based on data with available analytical values.

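### The logistic model for immune response does not define a vaccine-versus-placebo effect, because the placebo arm has no dose or strategy level

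*Protocol*

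**What the plan says.** Section 6.10.5(4) sets the outcome: "The outcome variable (Y) will be the presence or absence of humoral/cellular immunity". The independent variables include "vaccination dose (high vs. low), immunization strategy (combined vs. DNA-alone), smallpox vaccination history (vaccinated vs. unvaccinated), and study group (vaccine vs. placebo"). The sentence before it, which lists the comparisons, explains dose in brackets as combined versus DNA-alone, so dose and strategy are mixed there too. The section opens with a limit on its own role: "Immunogenicity evaluation will primarily be descriptive, reporting the positive rates of humoral and cellular immune responses".

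Section 6.10.2 fixes the size ("this Phase Ib study will enroll 36 healthy volunteers") as a regulatory requirement, with no power calculation. In section 6.4.2 the combined group is "further divided into a low-dose and a high-dose subgroup, each consisting of 12 individuals", with 6 people on DNA alone and 6 on placebo. Table 5 puts all 6 DNA-only participants on 4 mg.

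Section 6.10.7 says that "missing values will not be imputed". Section 6.10.6 sets a 5% level and asks for a p-value for every test.

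For adverse events, section 6.10.5(3) uses chi-square when incidence is higher and, "for those with very low incidence rates, statistical testing based on the Poisson distribution will be conducted". Fisher's exact test appears only in section 6.10.5(2), for baseline data, where the small sample is given as the reason.

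**The concern.** Dose and strategy are properties of the vaccine arms. A regression that also carries a vaccine-versus-placebo term needs a dose and a strategy value for people who have neither, and the protocol does not supply one. The choice of value decides which comparison the study-group coefficient makes. If it is made after results are known, it can move the p-value across 5%.

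The second weakness is that HIV-specific responses may well be absent in 6 placebo recipients. Ordinary maximum likelihood then has no finite solution for that term, and the protocol names no method for this case.

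The adverse-event rule has a related but smaller weakness. The test is chosen by an undefined incidence level, and chi-square is applied to an arm of 6, although the protocol's own small-sample reasoning already led it to Fisher's test for baseline data.

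**Working it through.** **Inputs from the protocol.** Arms: L = 2 mg + rTV (12), H = 4 mg + rTV (12), D = 4 mg DNA alone (6), P = placebo (6). Check: two phases of 18 at 2:1 give 12 + 6 and 12 + 6 = 36. The protocol gives no response rate, so the responder counts below are illustrations. The smallpox term is omitted throughout.

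**1. Placebo missing on dose and strategy.** A regression drops records with a missing covariate. All 6 placebo records go, study group is constant, and the design has rank 3 for 4 columns (intercept, dose, strategy, study group). The effect cannot be estimated.

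**2. Placebo given a code.** Code dose as 1 = high and strategy as 1 = combined, and give placebo dose d and strategy s. With L, H, D, P now standing for the arms' log odds, the study-group coefficient is

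L + d(H − L) − (1 − s)(H − D) − P.

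Take 9/12, 10/12, 2/6 and 1/6 responders, with odds 3, 5, 0.5 and 0.2. The variance of each log odds is 1/responders + 1/non-responders: 0.444, 0.600, 0.750 and 1.200.

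| Placebo coded as | Contrast | Odds ratio | SE (log) | Wald p |
|---|---|---|---|---|
| low, DNA-alone | L − H + D − P | 3 × 0.5 / (5 × 0.2) = 1.5 | √2.994 = 1.73 | 0.81 |
| high, DNA-alone | D − P | 0.5 / 0.2 = 2.5 | √1.950 = 1.40 | 0.51 |
| low, combined | L − P | 3 / 0.2 = 15 | √1.644 = 1.28 | 0.035 |
| high, combined | H − P | 5 / 0.2 = 25 | √1.800 = 1.34 | 0.016 |

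The first row describes 2 mg DNA alone, a regimen that the trial does not give. For comparison, Fisher's test on 21/30 v 1/6 gives p = 0.024.

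**3. No placebo responders.** The chance of 0/6 is (1 − p)^6. At true placebo rates of 0, 1, 5 and 10% it is 1.00, 0.94, 0.74 and 0.53. With 9/12, 10/12, 2/6 and 0/6, and placebo coded low, DNA-alone, the iterations do not settle: the coefficient is 8.0 (SE 25), 15.0 (SE 817) and 25.0 (SE about 121,000) after 8, 15 and 25 steps. The Wald p-value at the last step is 0.9998. Fisher's test on 21/30 v 0/6 gives p = 0.003.

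The likelihood-ratio test remains usable on the same data but still follows the code: p = 0.18 (low, DNA-alone), 0.07 (high, DNA-alone), 0.0007 (low, combined) and 0.0002 (high, combined).

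**4. Adverse-event tests.** In an arm of 6 the expected counts with and without an event add up to 6, so they can never both reach 5. Full enumeration of the uncorrected chi-square test at a nominal 5% gives a true size of at most 6.7% for 12 v 6. For 24 v 6 it is 5.3%, 4.4%, 4.1% and 5.3% at event rates of 15, 20, 30 and 50%. Fisher's test stays at or below 2.7% for 12 v 6 and 2.4% for 24 v 6.

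**The case against.** The strongest reply is that coding belongs to a statistical analysis plan, which section 5.3 assigns to the data management center and which is not shown. The protocol says that the variables include these four and does not state outright that all enter one model. A sensible code also exists. Setting placebo at the vaccine recipients' average (d = 18/30 = 0.6, s = 24/30 = 0.8) makes the coefficient 0.4L + 0.4H + 0.2D − P, a participant-weighted average. In the illustration that is exp(0.4 ln 3 + 0.4 ln 5 + 0.2 ln 0.5 − ln 0.2), or about 12.9. This stands as a reason not to say that the model can never yield a vaccine effect. It does not remove the gap: the protocol fixes the variables, nothing in it points to that code, and the simple codes disagree.

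A reader might infer that a strong vaccine response would be reported as non-significant. The documents do not support that. They name no Wald test, and the positive rates, such as 21/30 and 0/6, would be reported in any case.

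A reader might also infer that the adverse-event tests are badly miscalibrated. Chi-square for 24 v 6 does reach 9.0%, but near a 5% event rate, where section 6.10.5(3) would probably not use chi-square. The Poisson test's form is not stated, so no size can be assigned to it.

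Finally, the plan for intensity data, "For immune response intensity indicators such as antibody titers and Elispot counts, repeated measures ANOVA will be used", might be read together with the no-imputation rule as deleting everyone with a missed sample. Section 6.10.7 goes on to base results on available values, and listwise deletion is stated nowhere, so that inference is not supported either.

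**Conclusion.** The point holds in a limited form. As specified, the regression does not define which vaccine-versus-placebo comparison it makes, and its result can range from clearly non-significant to significant on identical data. The odds ratios of 1.5 to 25 rest on illustrative counts. The dependence on coding does not: it follows from the four arms and the listed covariates.

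The breakdown under 0/6 is conditional on that outcome, which is more likely than not at any true placebo rate up to 10%. It makes a Wald p-value uninformative but leaves a likelihood-ratio or exact test usable.

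The adverse-event issue is a modest inconsistency in where Fisher's test is allowed. Since immunogenicity is primarily descriptive and a secondary objective (section 6.1), the whole is a moderate matter. It should be settled before unblinding but does not threaten the trial's main safety description.

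**What to change.** In section 6.10.5(4), replace the dose, strategy and study-group terms with arm as one four-level factor. Name the contrasts: each vaccine arm v placebo; 4 mg + rTV v 4 mg DNA-only (strategy); and 4 mg + rTV v 2 mg + rTV (dose). Keep smallpox history as a covariate or stratum. Use Fisher's exact test or exact logistic regression, with exact 95% confidence intervals. Remove the bracket that explains dose as combined versus DNA-alone.

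In section 6.10.5(3), extend the Fisher option of section 6.10.5(2) to comparisons of participants with adverse events, in place of the incidence-dependent choice between chi-square and Poisson.

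The cost is wording only: no participant, visit or sample changes, and standard SAS procedures suffice. The downside is that exact tests are conservative in arms of this size and their intervals are wider.

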### (5) Exploratory Analysis:

Certain subject characteristics, such as gender and ethnicity, may influence study outcomes.

Therefore, identifying factors affecting vaccine safety and immunogenicity is an important aspect of exploratory analysis.

#### **6.10.6 Hypothesis Testing and Significance**

All statistical tests will be conducted at a 5% significance level. P-values will be provided for all hypothesis tests.

#### **6.10.7 Treatment of Missing Values**

In statistical analysis, missing values will not be imputed. Unless otherwise specified, all results are based on data with available analytical values.

#### **6.10.8 Statistical Analysis Software**

In this report, unless otherwise specified, all analysis results were generated using the licensed SAS 9.1.3 software. The software SITE number is: 47174001.

## **7 Management of Clinical Trial**

### **7.1 Data Management**

#### **7.1.1 Data Management of the Clinical Study Site**

The clinical trial unit is responsible for meticulously documenting the subjects' raw data sheets, preserving all test reports within these sheets, and ensuring they include the subject's identification number, specimen collection date, and the examiner's signature. In instances where test results are abnormal, it is imperative to note whether any measures have been taken, the date the report was reviewed, and the signature of the reviewing physician. Any alterations to the test results must be signed off by the research personnel and the date of the change recorded.

Researchers are required to accurately complete the Case Report Forms (CRFs) and transmit them to the clinical data management center. Upon receiving the data quality control report from the data center, researchers should promptly address any queries and make necessary amendments on the original report forms before faxing them back to the data center.

In compliance with the "Good Clinical Practice" guidelines issued by the National Medical Products Administration, the clinical trial unit must securely store all research materials from the trial phase, including original data sheets of subjects, laboratory result reports, original signed informed consent forms, CRFs, detailed treatment records, and other hospital original records, under dual-lock security by designated personnel until five years after the termination of the clinical trial. A list of materials that the clinical trial unit is required to retain can be found in Appendix 7.

#### **7.1.2 Sponsor's Data Management**

In accordance with the "Good Clinical Practice for Drugs" regulations issued by the National Medical Products Administration, the NCAIDS Clinical Trial Management Core will designate specific personnel to securely store all documentation related to the application, approval, execution, and completion phases of clinical trials (detailed contents are listed in

Appendix 7) under dual-lock security. These documents will be retained until five years after the product in question is marketed or the product development is officially terminated.

### **7.1.3 Ownership of Study Data**

All documentation pertaining to this clinical study is the property of the NCAIDS and the Beijing Institute of Biological Products. Except as required by the National Medical Products Administration, clinical researchers are prohibited from providing any form of this information to third parties without the written consent of the sponsor.

